### Statistical analysis

2.10

Statistical analyses will be implemented by SPSS 17.0 and Microsoft Excel 2007 software. Data will be represented as mean ± standard deviation (SD). We will use a 2-way repeated measurement analysis of diversification (group × time) to compute the impact of joint mobilization techniques, physical modality therapy, and the control process, which involve the preliminary and final intervention effects. If subjects fail to make a follow-up, we will use an intention-to-treat analysis. A *t*-test will be performed to compare the changes in measures within groups. Statistical significance will be considered at *P* < .05.

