### Study method

2.2

We will design a single-blind RCT to compare the effects of joint mobilization techniques and physical modality therapy with usual care on TKA patients. A total of 120 patients with early postoperative TKA will be enrolled and investigated in Shanghai Shangti Orthropedic Hospital, Shanghai City, China.

All subjects will receive a questionnaire before the study. The questionnaire will include the following: basic information (eg, age), history of injury, pain (visual analog scale, VAS), knee function [the knee joint Hospital for Special Surgery (HSS) score], and Pittsburgh Sleep Quality Index (PSQI). All participants will sign a consent form before the study.

Subjects who meet the inclusion criteria divided into a 1:1:1 ratio will be randomly selected. After the random distribution, patients with early postoperative TKA will be distributed to a control group (regular training), a physical modality therapy group (physical therapy with regular training), and an intervention group (mobilization with regular training). The study period will last 6 months, including a 4-week intervention and follow-up of 2 to 6 months without intervention. Before intervention, evaluation will be conducted during the 2nd and 4th weeks and during the 3rd and 6th months.

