### Participants

2.3

Inclusion criteria include the following:1.50 to 80 years old.2.With a diagnosis of knee osteoarthritis symptoms and surgical indications.3.Underwent first unilateral total knee replacement.4.With the same operation method, normal blood clotting index.5.Conscious and without cognitive impairment.6.Not more than 2 weeks after TKA.

Exclusion criteria include the following:1.With serious cardiovascular disease, neurological disease, osteoporosis and metabolic disease.2.Suffering from hemophilia, sever diabetes, tumor, or function of blood coagulation disorder.3.With fracture, dislocation, abnormal structure, and other surgeries.4.Inability to communicate in Chinese.

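### The group × time ANOVA names no baseline covariate, although baseline VAS, HSS and PSQI are collected; adjusting for them would sharpen every between-arm contrast at a given visit

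*Protocol article*

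**What the plan says.** The Statistical analysis section fixes the efficacy model: "We will use a 2-way repeated measurement analysis of diversification (group × time"), applied to the three arms, "which involve the preliminary and final intervention effects". It names no covariate. The one further test compares nothing between arms: a t-"test will be performed to compare the changes in measures within groups". The threshold is given as "Statistical significance will be considered at *P* < .05".

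The Study method section has all subjects complete a questionnaire before the study. It covers "pain (visual analog scale, VAS), knee function [the knee joint Hospital for Special Surgery (HSS) score"), and also the PSQI. Evaluations follow at weeks 2 and 4 and months 3 and 6. On size: "A total of 120 patients with early postoperative TKA will be enrolled", allocated 1:1:1, so 40 per arm.

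The Research object section asks two efficacy questions: whether mobilization helps, and whether it does better than physical modality therapy. Both are between-arm questions.

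**The concern.** The word preliminary in the description of the model suggests that the pre-treatment score is one level of the time factor. That has two consequences.

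- **Group main effect.** It averages over all occasions, including one before treatment. With baseline plus four later visits, an effect of constant size d after baseline contributes only (4/5)d = 0.8d to the averaged difference.
- **Group × time interaction.** If only two occasions are used (before and after), this test is exactly a comparison of change from baseline between arms. That is valid, but less precise than a comparison adjusted for baseline.

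With 40 per arm, precision matters. The article's own Strengths and limitations section lists the number of patients as a limitation. The scores needed for adjustment are already collected, so precision is being left unused.

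**Working it through.** The article gives no effect size, SD, between-visit correlation or power target, so there is no figure of its own to reproduce.

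**Inputs from the article:** 120 patients allocated 1:1:1, so n = 40 per arm; threshold .05; baseline VAS, HSS and PSQI collected.

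**Assumptions:** two-sided tests; the same SD (set to 1) at baseline and follow-up; correlation r = 0.3, 0.5 or 0.7 between baseline and the visit tested; complete data; a 0.6 SD difference between two arms at that visit.

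**Step 1: residual variance per patient.** For change from baseline it is 2(1 − r). For follow-up adjusted for baseline (ANCOVA) it is 1 − r² = (1 − r)(1 + r). The ratio of the second to the first is (1 + r)/2.

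| r | Change, 2(1 − r) | ANCOVA, 1 − r² | Ratio | Change-score N matching 120 with ANCOVA |
|---|---|---|---|---|
| 0.3 | 1.40 | 0.91 | 0.65 | 120/0.65 ≈ 185 |
| 0.5 | 1.00 | 0.75 | 0.75 | 120/0.75 = 160 |
| 0.7 | 0.60 | 0.51 | 0.85 | 120/0.85 ≈ 141 |

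**Step 2: power for one pair of arms at one visit, like for like.** The noncentrality is 0.6/√(2 × variance/40). Residual variance is pooled over the three arms, giving 117 df for change and 116 for ANCOVA, with the noncentral t distribution.

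| r | Noncentrality, change | Power, change | Noncentrality, ANCOVA | Power, ANCOVA |
|---|---|---|---|---|
| 0.3 | 2.27 | 61% | 2.81 | 80% |
| 0.5 | 2.68 | 76% | 3.10 | 87% |
| 0.7 | 3.46 | 93% | 3.76 | 96% |

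The gain is about 18, 11 and 3 percentage points (from unrounded powers). It comes from baseline adjustment alone, since the visit, the pair of arms and the significance level are the same in both columns.

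**Step 3: against the five-visit omnibus tests.** Here the interaction has (3 − 1)(5 − 1) = 8 and 468 df, and the group main effect 2 and 117 df, under compound symmetry. The comparator is the week-4 ANCOVA contrast of mobilization vs usual care. Effects are in SD at week 2/week 4/month 3/month 6.

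| Assumed effect of mobilization | Laser effect | r | Interaction | Main effect | Week-4 ANCOVA contrast |
|---|---|---|---|---|---|
| 0.4/0.6/0.3/0.1 (peaks at week 4) | half | 0.5 | 53% | 28% | 87% |
| 0.1/0.3/0.6/0.6 (delayed) | half | 0.5 | 69% | 35% | 34% |
| 0.6 throughout | none | 0.3 | 63% | 92% | 80% |
| 0.6 throughout | none | 0.7 | 97% | 71% | 96% |

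The order of the tests changes with the shape of the effect and with r. Only the gain in Step 2 keeps its sign.

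**The case against.** **The article is condensed.** It does not say outright that baseline is a level of time, nor that covariates are excluded, and a full analysis plan may add them. This stands in part. But the article does commit to a named model, and the point is an improvement to that stated model rather than a complaint about missing detail.

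**A large loss of power.** A reader might infer that the planned ANOVA loses a great deal, for example 53% or 28% against 87% in the first row of the last table. The article does not support this. That row sets three-arm omnibus tests against one chosen pair at one chosen visit, under an effect assumed to peak there. The article gives no effect shape and names no primary visit, and with a delayed or sustained effect the order can reverse. The week-4 contrast is also no cure for the second efficacy question: in that same row, mobilization vs laser (a 0.3 SD difference) has only about 34% power even with adjustment.

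**Uncorrected baseline imbalance.** A group × time test that includes baseline does take baseline into account, because it compares change. It does so less efficiently than ANCOVA.

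**Days since surgery.** The entry rule, "Not more than 2 weeks after TKA", might suggest that time since operation is a neglected prognostic covariate. The article gives no prognostic strength for it and does not list it as a recorded variable, so no gain can be claimed.

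**Inflated type I error.** This would follow only if the interaction were tested without a sphericity correction. The article does not say so, and such detail is commonly left to the analysis plan.

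**Conclusion.** The point holds for baseline adjustment and no further. As worded, the model leaves collected baseline scores out as covariates. Using them would cut the variance of a between-arm contrast at a given visit to 0.65–0.85 of the change-score variance for r between 0.3 and 0.7. At 40 per arm and an assumed 0.6 SD effect, power at a given visit rises by about 18 points at r = 0.3, 11 at r = 0.5 and 3 at r = 0.7.

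These sizes rest on equal SDs across visits, complete data and the assumed correlation and effect, none of which the article states. They also rest on reading baseline as part of the time factor, which is natural but not explicit. The planned test is not invalid; it is less precise than the collected data allow. Whether a single-visit contrast would beat the five-visit omnibus tests cannot be settled from the article.

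**What to change.** For outcomes measured at baseline, replace the group × time ANOVA with a mixed model for the post-baseline visits (weeks 2 and 4, months 3 and 6). Its terms are arm, visit, arm × visit and baseline value × visit. Report two baseline-adjusted contrasts, mobilization vs usual care and mobilization vs physical modality therapy, at one visit that the investigators choose and record before the data are seen. That choice is a separate trade-off, since it gives up power against effects that appear at other times, and it should be made on the trial's aims.

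The cost is a change to the analysis wording. No new patients or visits are needed, and no new measurements for VAS, HSS and PSQI.

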**Methods/Design::**

We will manage a single-blind, prospective, randomized, controlled trial of 120 patients with unilateral TKA. Patients will be randomized into an intervention group, a physical modality therapy group, and a usual care group. The intervention group will undergo joint mobilization manipulation treatment once a day and regular training twice a day for a month. The physical modality therapy group will undergo physical therapy once a day and regular training twice a day for a month. The usual care group will perform regular training twice a day for a month. Primary outcome measures will be based on the visual analog scale, the knee joint Hospital for Special Surgery score, range of motion, surrounded degree, and adverse effect. Secondary indicators will include manual muscle testing, 36-Item Short Form Health Survey, Berg Balance Scale function evaluation, Pittsburgh Sleep Quality Index, proprioception, and muscle morphology. We will direct intention-to-treat analysis if a subject withdraws from the trial.

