### Exit criteria and management

2.4

Early postoperative TKA patients will be allowed or be required to quit the study if1.Subject has a demand.2.Subject develops a serious disease (eg, heart disease).3.Subject experiences side effects with the treatment.

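### Intention-to-treat is invoked only if patients are lost, and the named repeated-measures ANOVA, run as written without imputation, leaves those patients out

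*Protocol article*

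**What the plan says.** Section 2.10 (Statistical analysis) names the between-group method: "We will use a 2-way repeated measurement analysis of diversification (group × time"), where the context shows that analysis of variance is meant. It adds that the comparison covers effects "which involve the preliminary and final intervention effects". The software is SPSS 17.0 with Excel 2007.

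On patients who are lost, the same section says "If subjects fail to make a follow-up, we will use an intention-to-treat analysis". The abstract (Methods/Design) says "We will direct intention-to-treat analysis if a subject withdraws from the trial". Nowhere does the article say that every randomized patient is analysed in the assigned arm regardless of dropout. It names no imputation and no model that keeps patients with incomplete data.

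Two other sections bear on the point. Section 2.2 (Study method) sets the assessments: "Before intervention, evaluation will be conducted during the 2nd and 4th weeks and during the 3rd and 6th months". The sensible reading is a baseline plus four later visits. Section 2.4 (Exit criteria and management) allows or requires a patient to leave on several grounds, one of them being "Subject experiences side effects with the treatment".

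**The concern.** Two different things have been run together. Intention-to-treat is a rule about the analysis set: all randomized patients, each in the arm assigned. It applies from randomization onward and does not start when someone drops out. It is also silent on what to do about an outcome that was never measured. The article presents it twice as the response to missing follow-up, so a slip of wording is an unlikely explanation.

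The named model makes this matter. A classical two-way repeated-measures ANOVA needs a value from each patient at every time point entered. A patient who misses one of them contributes nothing, not even the visits attended. The patients for whom intention-to-treat is invoked are therefore the ones whom this model leaves out, unless their values are filled in first.

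Two things are at stake. One is precision, because the analysed arms shrink. The other is the validity of the comparison. Side effects are a listed reason for leaving, so loss may be related to treatment and to outcome, and a comparison of completers is not protected by randomization against such loss.

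**Working it through.** The article gives no effect size, SD, power or expected dropout, so there is no stated figure to reproduce. What follows is an illustration on assumed rates.

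**Inputs from the article**
- 120 patients in total (section 2.2), allocated 1:1:1, so 120 / 3 = 40 per arm.
- Four post-baseline visits: weeks 2 and 4, months 3 and 6 (section 2.2).
- Significance level .05 (section 2.10). It does not say one- or two-sided; two-sided is assumed.

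**Assumed inputs**
- 5% or 10% of patients missing at any one visit, with baseline complete.
- Pairwise comparison of two arms by two-sample *t*-test, 80% power.

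**How many visits enter the ANOVA?** The phrase about preliminary and final effects in section 2.10 can mean two time points (baseline and one later visit) or the whole schedule. Both readings are shown.

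**Step 1: complete patients per arm**
- One post-baseline visit: 40 × (1 − m). For m = 5%, 40 × 0.95 = 38. For m = 10%, 40 × 0.90 = 36.
- Four post-baseline visits, misses independent: 40 × (1 − m)^4. For m = 5%, 40 × 0.815 = 32.6, about 33. For m = 10%, 40 × 0.656 = 26.2, about 26.

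**Step 2: standardized difference detectable with 80% power**

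| Patients per arm | How reached | Detectable difference |
|---|---|---|
| 40 | nobody lost | 0.63 SD |
| 38 | one visit, 5% missed | 0.65 SD |
| 36 | one visit, 10% missed | 0.67 SD |
| 33 | four visits, 5% missed at each | 0.70 SD |
| 26 | four visits, 10% missed at each | 0.79 SD |

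**Step 3: bias from selective loss in one arm.** Let a fraction p of one arm be lost, and let those patients be g SD worse than the rest. The full-arm mean lies p × g below the completers' mean, so the completers' mean is biased by p × g.
- p = 10%, g = 1: 0.10 × 1 = 0.10 SD.
- p = 20%, g = 1: 0.20 × 1 = 0.20 SD.

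A simulation gives a similar size. It assumed no true effect, 40 per arm, five visits with a within-patient correlation of 0.6, and the worst-scoring patients of one arm at week 2 leaving after that visit. Over 4000 runs, the month-6 completers' difference favoured that arm by about 0.11 SD with 10% leaving and 0.20 SD with 20% leaving.

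**The case against.** The strongest reply has four parts.

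First, the two statements are compatible. One can keep all randomized patients in their arms, impute the missing values, and then run the ANOVA. This stands. A reader might infer that the plan contradicts itself outright, or that a completers' analysis is certain, and the article supports neither. The exclusion follows only if the ANOVA is applied as written, with no imputation and no other model substituted.

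Second, a journal article may leave imputation and sensitivity analyses to a fuller document, so silence on them is no fault. This also stands, but it does not reach the point. The conditional rule is stated, not omitted, and an analysis plan that followed it would inherit it.

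Third, the loss of precision may be modest. If only two time points enter, 36 to 38 of 40 per arm remain. If all visits enter, the independence assumption overstates the loss, because the same patients tend to miss several visits. Both remarks are fair, and the four-visit figures belong at the harsh end.

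Fourth, nothing in the article shows that poor recoverers leave, or that they leave more often from one arm. Section 2.4 gives exit reasons without rates, and all three arms train twice a day. A reader might infer differential loss as a fact. The side-effect exit makes outcome-related loss possible, and no more can be said from the document.

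**Conclusion.** The concern holds in a limited form. Both statements of intention-to-treat are wrong as written: they make it conditional on loss and treat it as a way of handling missing data. The named ANOVA, applied without imputation, does not honour the promise for patients who lack a time point that enters it.

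The size cannot be established, because no dropout rate is given. Under the assumed 5% to 10% missed per visit, the loss runs from slight (0.65 to 0.67 SD detectable, against 0.63 SD) to material (0.70 to 0.79 SD), depending on how many visits enter. A bias of 0.10 to 0.20 SD needs 10% to 20% of one arm to be lost and to be 1 SD worse than the rest. It shows what is possible and is not a forecast. The wording and the choice of model should be settled before analysis, because a method for filling in values that is picked after the data are seen would be open to challenge.

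**What to change.** 1. In the abstract and in section 2.10, replace the conditional sentence with an unconditional one: *All randomized patients are analysed in the arm assigned.*
2. Replace the complete-data ANOVA with a likelihood-based mixed model for repeated measures, with group, time and group × time as terms, fitted to all available visits of every randomized patient. Multiple imputation before the ANOVA is a defensible alternative if the team prefers to keep that model. State which time points enter.
3. Add one sensitivity analysis for informative dropout, for example imputing mobilization-arm dropouts from the usual-care arm, because the mixed model itself relies on the observed data to account for the loss.

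The cost is a change of wording and slightly more analysis work. The planned software has a mixed-model procedure. Design, visits and sample size stay as they are.

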### Research object

2.1

We will accomplish an RCT on the effect of joint mobilization techniques for primary TKA to determine the following:1)Whether mobilization benefits the rehabilitation of primary TKA.2)Whether mobilization exerts better effects than physical modality therapy for primary TKA.3)The side effects associated with mobilization.

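### Neither test named in section 2.10 directly answers the pairwise questions: the ANOVA is a three-arm omnibus test, and the t-test looks only within arms

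*Protocol article*

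**What the plan says.** Section 2.10 (Statistical analysis) names two tests. The first is the repeated-measures ANOVA: "We will use a 2-way repeated measurement analysis of diversification (group × time) to compute the impact of joint mobilization techniques", with the other two arms listed alongside. The second is a t-test, described in these words: "to compare the changes in measures within groups". One threshold is given for everything: "Statistical significance will be considered at *P* < .05". No comparison of one arm with another is named.

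The questions are set out elsewhere. Section 2.1 (Research object) asks "Whether mobilization benefits the rehabilitation of primary TKA" and then "Whether mobilization exerts better effects than physical modality therapy for primary TKA". The first does not name its comparator, but section 2.2 (Study method) says that both treatments are compared with usual care. The closing summary in section 3.1 again asks whether mobilization does better than physical modality therapy or usual care.

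On size, section 2.2 states "A total of 120 patients with early postoperative TKA will be enrolled", allocated 1:1:1. Section 2.3 admits patients up to 2 weeks after surgery. Section 2.8 has every arm do regular training for 20 minutes twice a day for 4 weeks.

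**The concern.** The objectives need two differences between arms, and neither named test isolates one.

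- **The ANOVA.** With three arms, a significant group × time term says that the time courses are not all alike. It does not say which pair differs. The difference could lie in the physical modality arm alone.
- **The within-group t-test.** It asks whether one arm changed from its own baseline. All patients start soon after surgery and all train twice daily, so that change contains recovery and training as well as any effect of mobilization. The randomized comparison plays no part in it.

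At stake is what the trial may conclude. A report that combines a significant interaction with a significant improvement in the mobilization arm could look like support for mobilization even when mobilization equals usual care.

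**Working it through.** The article states no power, effect size or SD, so there is no figure of its own to reproduce. The check asks how the named tests behave when mobilization has no effect beyond usual care.

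**Inputs from the article.** N = 120 and 1:1:1 allocation (section 2.2), so 120/3 = 40 per arm. The threshold is P < .05 (section 2.10). Its sidedness is not stated, and two-sided is assumed here.

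**Assumed input.** Standardized recovery dz = mean change / SD of change, the same in every arm, at 0.3, 0.5 and 0.8.

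**Step 1: within-arm t-test, no difference between arms.** The test has 39 degrees of freedom and critical value t = 2.023. The smallest observed change that reaches significance is 2.023/√40 = 0.32 SD. The probability p that one arm is significant comes from the noncentral t distribution with noncentrality dz × √40. Because the arms are independent:

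- all three arms significant: p³
- mobilization significant and usual care not: p(1 − p)

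| dz (assumed) | Noncentrality | One arm significant, p | All three, p³ | Mobilization yes, usual care no, p(1 − p) |
|---|---|---|---|---|
| 0.3 | 1.90 | 0.457 | 0.095 | 0.457 × 0.543 = 0.248 |
| 0.5 | 3.16 | 0.869 | 0.657 | 0.869 × 0.131 = 0.114 |
| 0.8 | 5.06 | 0.9985 | 0.996 | 0.9985 × 0.0015 = 0.0015 |

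With large recovery every arm is significant and the test does not discriminate between arms. With modest recovery the arms often disagree by chance.

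**Step 2: between-group tests under the same null.** Change scores were simulated in 20,000 trials with 40 per arm, at recovery of 0.5 and 1.0 SD. The three-group test of change rejected in 5.0% of trials at both. A direct mobilization versus usual care test rejected in 4.8% and 5.3%. Both hold their level whatever the recovery.

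**Step 3: only the physical modality arm differs.** Recovery was set at 1 SD in all arms, with a further 0.7 SD in the physical modality arm only (both assumed). The three-group test and the mobilization within-arm t-test were both significant in 90% of trials, although mobilization equalled usual care.

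**Step 4: what direct contrasts can detect.** With 40 per arm, the standardized difference d detectable with 80% power is (z for alpha + 0.842) × √(2/40), where √(2/40) = 0.2236.

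- Two-sided alpha 0.05: (1.960 + 0.842) × 0.2236 = 0.63. Power at d = 0.3, 0.5 and 0.8 is 0.27, 0.61 and 0.95.
- Two-sided alpha 0.025 (Bonferroni for two contrasts): (2.241 + 0.842) × 0.2236 = 0.69. Power at the same d is 0.18, 0.50 and 0.91.

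**The case against.** The strongest reply has three parts.

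**Missing detail is not a fault here.** The article condenses a fuller protocol, and pairwise contrasts after a three-arm ANOVA are often left to that document or to the SAP. This stands as far as it goes: the absence of contrasts alone would not be a finding. But the article also commits to a within-group test under a P < .05 rule, as the only test besides the ANOVA. That is a stated choice, and it does not suit comparative objectives.

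**The ANOVA does the comparative work.** Section 2.10 gives it that role, and it is a valid between-group test. A reader might infer that the second objective has no valid test at all, and the documents do not support that. The gap is narrower: the named test is an omnibus test and does not identify the pair. Nor does section 2.10 call the t-test a follow-up to the ANOVA or tie a conclusion about arms to it, so how a later report would use it is a risk and not something the plan states. When all arms are truly alike, the interaction test gives some protection, since it rejects in only about 5% of trials. When only the physical modality arm differs, it gives mobilization none (step 3).

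**Recovery may be small.** A reader might infer that the t-test is bound to be significant in every arm. The documents give no SD or expected change, and near-certainty needs about 0.8 SD. That is plausible for pain and the HSS score by 4 weeks, but nothing in the article shows it, least of all for proprioception, muscle thickness, sleep quality or manual muscle testing. At 0.3 SD all three arms are significant in only about 10% of trials. The two harms are alternatives that depend on the outcome, and they do not occur together.

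**Conclusion.** The point holds in a limited form and should be fixed before the analysis. As written, section 2.10 offers one valid but non-specific between-group test and one test that does not compare arms. Neither directly answers mobilization versus physical modality therapy or mobilization versus usual care.

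The size is illustrative. It rests on 40 evaluable patients per arm, two-sided 0.05, identical recovery across arms and the assumed range of 0.3 to 0.8 SD of change. Over that range, significance in a single arm with no treatment difference runs from about 46% to 99.9%, and the misleading split between mobilization and usual care falls from about 25% to 0.1%. The 90% figure for the physical modality scenario depends on its own assumed values of 1 SD and 0.7 SD.

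**What to change.** In section 2.10, report within-group changes descriptively, without tests. Base conclusions on two pre-specified between-arm contrasts from the repeated-measures model:

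1. mobilization minus usual care;
2. mobilization minus physical modality therapy.

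Estimate each at one named visit, for example week 4 (end of treatment), adjusted for baseline and with a 95% CI. Test them in that fixed order, or with a Holm or Bonferroni correction. The group × time test can stay as an overall summary.

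The cost is a few sentences of analysis wording and no new data or patients. In fixed order, the second contrast can be claimed only if the first is significant. Under Bonferroni, the difference detectable with 80% power rises from 0.63 to 0.69 SD. This rule covers the two contrasts for one outcome; multiplicity across the several primary indicators would need its own rule.

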### Measurement of outcomes

2.9

Tools to measure primary indicators include the following:1.The VAS is used to assess pain intensity. It has a length of 100 mm and a pain scale of 0 to 10, where 0 represents no pain and 10 represents unbearable pain. The pain intensity is determined by the patient.^[25]^2.The knee joint HSS score, with a 100-point scoring system, is used to gauge knee function. It applies the following criteria: pain, 30 points; function activity, 22 points; range of motion, 18 points; muscle strength, 10 points; flexion deformity, 10 points; and stability, 10 points. A score of ≥85 points is equivalent to best, 70–84 to good, 60–69 to medium, and ≤59 points to poor. The HSS score has become the gold standard to evaluate knee arthroplasty.^[26]^3.Adverse events associated with joint mobilization technique that will be recorded.

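### The primary outcomes are listed two ways and share one P < .05 with no deciding outcome, visit or contrast, so the false-positive risk is about 9% to 18.5%, not 5%

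*Protocol article*

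**What the plan says.** The Methods/Design part of the abstract bases the primary outcome measures on "the visual analog scale, the knee joint Hospital for Special Surgery score, range of motion, surrounded degree, and adverse effect". Section 2.9 gives a shorter list. It opens with "Tools to measure primary indicators include the following:1.The VAS is used to assess pain intensity", continues with the HSS score, and ends with "Adverse events associated with joint mobilization technique that will be recorded". In that section range of motion appears only inside the HSS score ("pain, 30 points; function activity, 22 points; range of motion, 18 points"), and surrounded degree does not appear.

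On arms: "Patients will be randomized into an intervention group, a physical modality therapy group, and a usual care group". On visits, section 2.2 says that "evaluation will be conducted during the 2nd and 4th weeks and during the 3rd and 6th months". Section 2.1 asks whether mobilization helps, without naming a comparator, and whether it does better than physical modality therapy.

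Section 2.10 states one between-group analysis, a two-way (group × time) repeated-measures analysis of variance, plus t-tests of change within groups. The only decision rule is "Statistical significance will be considered at *P* < .05". No outcome, visit or contrast is ranked first, and success on all primaries is not required.

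**The concern.** With several outcomes of equal primary rank and a 5% test on each, a significant result on any one of them can be reported as a positive trial. The 5% level then describes each test, not the trial's conclusion. Because the two lists differ, it is also unclear how many outcomes are in the family, so a multiplicity method specified elsewhere would not know what to adjust for.

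A second gap concerns the contrast. The stated test asks whether three profiles over time differ somewhere, whereas the objectives ask about mobilization in particular. Getting from one to the other needs a pairwise comparison, and the protocol does not say which or when. At stake is whether the outcome, visit and pair of arms behind the headline claim can be chosen after the data are seen.

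**Working it through.** **Inputs from the protocol.** Level 0.05 per test (2.10). 120 patients at 1:1:1, so 120/3 = 40 per arm (2.2). Baseline plus four later visits (2.2). Efficacy primaries: two under section 2.9 (VAS, HSS), or four under the abstract (adding range of motion and surrounded degree).

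**Assumptions.** No true effect, normal data, all efficacy outcomes continuous, equal correlation between visits (0.6), correlation between outcomes 0 to 0.7, two-sided pairwise tests. The protocol gives none of these.

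The plan states no trial-wide error rate to reproduce. As a check on its per-test level, the group × time test on a single outcome rejects in about 5% of simulated trials.

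**Step 1: stated test only, independent outcomes.** Chance of at least one false positive = 1 − 0.95^k.
- k = 2: 1 − 0.9025 = 9.8%
- k = 4: 1 − 0.8145 = 18.5%

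**Step 2: stated test only, correlated outcomes.** Simulation, 20,000 trials per setting, one group × time F test per outcome:

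| Outcome correlation | Two outcomes | Four outcomes |
|---|---|---|
| 0 | 9.7% | 18.5% |
| 0.5 | 9.0% | 16.4% |
| 0.7 | 8.5% | 14.1% |

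**Step 3: does the stated test answer objective 2?** With three arms and five time points, the interaction has (3 − 1) × (5 − 1) = 8 degrees of freedom. A significant result says that the three profiles are not parallel. A difference between physical modality and usual care alone could produce it, so it does not show that mobilization beats physical modality.

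**Step 4: hypothetical worst case, not stated in the protocol.** Suppose mobilization were also compared with each other arm at each of the four visits, at .05. That is 2 × 4 × 2 = 16 tests for two outcomes and 4 × 4 × 2 = 32 for four. With visit correlation 0.6 and outcome correlation 0.5:

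| Counted as a false positive | Two outcomes | Four outcomes |
|---|---|---|
| Result favouring mobilization | about 21% | about 33% |
| Result in either direction | about 41% | about 61% |

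Varying the visit correlation from 0.4 to 0.8 moves the first row from 24% to 17% and from 37% to 27%. It moves the second row from 46% to 34% and from 67% to 51%.

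**Step 5: after the fix.** With a fixed order of two contrasts on one outcome and visit, the second is tested only if the first is significant. If the first null is true, any false claim requires rejecting it, which has probability 5%. If only the second null is true, falsely rejecting it has probability at most 5%. The pair is therefore held at 5%.

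**The case against.** The strongest reply is that the stated plan is narrower than its lists suggest. The group × time analysis pools arms and visits into one test per outcome, and the only t-test mentioned is within groups. Adverse events are to be recorded, with no test tied to them. Under section 2.9 two efficacy primaries remain, and 9% to 10% is a modest excess over 5%. Contrasts and their adjustment are also commonly left to an analysis plan, which is not shown.

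Most of this stands, and it rules out three stronger readings.
- A reader might multiply five outcomes, four visits and three pairs into 5 × 4 × 3 = 60 tests, which if independent would give 1 − 0.95^60 = 95.4%. The protocol states no per-visit pairwise tests, so even the figures of Step 4 are only a warning about what is left open.
- A reader might take all five listed primaries and quote 1 − 0.95^5 = 22.6%. The count of five is in the abstract alone, and adverse events are not an efficacy success.
- A reader might think that the overlap between outcomes makes matters worse, since pain and range of motion are 30 + 18 = 48 of the 100 HSS points. Overlap makes the tests positively correlated, which lowers the inflation, as Step 2 shows. It means only that agreement among these outcomes is weak confirmation.

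The reply does not remove the core. Which outcome is primary is a protocol decision. This protocol makes it twice, differently, and attaches the same unadjusted level to every outcome on either list. An unseen analysis plan could add an adjustment but could not tell which list to adjust.

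**Conclusion.** The point holds in limited form. The two lists of primary outcomes disagree, several outcomes share P < .05, and no outcome, visit or contrast leads. On the stated omnibus test alone, the chance of at least one false-positive efficacy primary is about 9% to 10% for two outcomes and about 14% to 18.5% for four. These figures assume no true effect, continuous normal outcomes, and a correlation between outcomes of 0.7 down to 0. The excess over 5% is present across that whole range; only its size depends on the assumptions. Separately, the omnibus test does not settle objective 2.

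The larger figures, about 21% to 33% in favour of mobilization or about 40% to 60% in either direction, apply only if per-visit pairwise tests at .05 are added. The protocol does not say that they will be.

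**What to change.** 1. Make the abstract and section 2.9 give the same primary outcomes, and say what surrounded degree measures if it stays.
2. Name one primary efficacy outcome and one visit. HSS total at week 4, the end of the intervention, is one example. VAS would also serve, as section 2.2 lists both in the questionnaire before the study.
3. Test mobilization against usual care at two-sided .05. Section 2.1 names no comparator for its first question, but section 2.2 presents usual care as the reference. Only if that test is significant, test mobilization against physical modality at .05.
4. Report adverse events as safety, and the other outcomes and visits as supportive.

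Alternatively, keep the efficacy primaries, with one prespecified test for each, and apply Holm across them. The ordered p-values are compared with .025 and .05 for two outcomes, or with .0125, .0167, .025 and .05 for four. The mobilization contrasts still need a stated order.

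The cost is wording in the protocol, and in the registration if it carries the same lists; no extra data are collected. The downside is that significant results on the other outcomes become supportive rather than confirmatory. Whether 40 per arm gives enough power for the chosen primary cannot be judged from this article and should be checked when the choice is made.
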